**Fig. 2 Fig2:**
[figure not shown]
A flowchart of the recruitment procedure of the study

Follow up will be carried out 3 months after the initial invitation to the study. All participants will be sent an email invitation including a link to a follow-up questionnaire aiming to investigate the primary and secondary outcomes. Two reminders, 1 week apart, will be sent to non-responders, also by email. In addition, participants who still do not respond, will receive an SMS every second day for 6 days (that is three additional reminders) These SMS will only include a single question investigating the primary outcome (weekly consumption). Finally, those not responding to the SMS will be contacted by telephone (maximum of 10 calls). Again, only the primary outcome will be investigated.

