### Statistical analyses

The baseline characteristics of responders will be compared between randomized groups using the chi-squared test or Fisher’s exact test for comparison of proportions, and Student’s *t* test for comparison of means. All outcome analyses will be compared between the two randomized groups (both with the same follow-up time) under the intention-to-treat principle (that is, all randomized individuals will be included in their originally randomized groups).

Total weekly consumption, eBAC and the number of negative consequences will be assessed for skewness by visual inspection of histograms or Q-Q plots. If skewed, they will be either log-transformed and analysed with linear regression or analysed with negative binomial regression. Frequency of HED occasions will be analysed by ordered logistic regression. All regression analyses will first be performed unadjusted, and then will be adjusted for weekly alcohol consumption at baseline, age, university and gender. If any of the baseline characteristics are significantly different between the two groups, further adjustment will be made to these covariates as well. The adjusted analyses will be the primary analysis. The data will be examined graphically for outliers. A sensitivity analysis excluding outliers will be performed.

Missing outcome data will be initially handled by a complete-cases analysis, which assumes that the data are missing at random (MAR). If data are not MAR, then non-responders differ systematically from responders and early responders are likely to differ systematically from late responders, who are likely to be similar to non-responders. Therefore, we will explore the plausibility of the MAR assumption by first regression of the primary outcome (weekly alcohol consumption) on the number of follow-up attempts needed before an individual responded.

Second, attrition will be investigated for significant differences between the study groups in completion of the follow-up questionnaire, and baseline characteristics will be compared between participants who do and do not respond at follow up. Any significant associations found could provide possible evidence against the MAR assumption.

Effect modification tests for total weekly consumption according to baseline, age, university, and gender will be undertaken for the primary outcome only. All analyses will be performed with two-sided tests with a 5% level of significance.

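### Differences in response by arm or baseline are read as evidence against MAR when they bear on MCAR, and the regression on attempts mixes late response with contact mode

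*Protocol article*

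**What the plan says.** All of the missing-data text is in the protocol article under Statistical analyses. The main analysis uses complete cases and is said to assume MAR. The reasoning for the checks is: "If data are not MAR, then non-responders differ systematically from responders and early responders are likely to differ systematically from late responders". Late responders are taken to resemble non-responders. Two sets of checks follow.

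- **Attempts:** "regression of the primary outcome (weekly alcohol consumption) on the number of follow-up attempts needed before an individual responded".
- **Response patterns:** the first looks at completion by arm: "attrition will be investigated for significant differences between the study groups in completion of the follow-up questionnaire". The second sets responders against non-responders on their baseline data: "baseline characteristics will be compared between participants who do and do not respond at follow up".

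The conclusion attached to them is: "Any significant associations found could provide possible evidence against the MAR assumption".

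The same section makes the adjusted analysis primary. The regressions are run unadjusted and "then will be adjusted for weekly alcohol consumption at baseline, age, university and gender", with further covariates only if they differ significantly between the arms.

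The contact sequence is under Participants and procedure. There is an email invitation with two email reminders, then three SMS, then up to 10 telephone calls. Of the SMS stage it says: "These SMS will only include a single question investigating the primary outcome (weekly consumption". The telephone stage also covers only the primary outcome. Under Outcome measures, that outcome is defined as a sum over the seven days of a typical week.

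**The concern.** MAR allows response to depend on anything observed. Arm and baseline characteristics are observed, so an association between them and response contradicts MCAR and leaves MAR untouched. The stated premise (not MAR implies that responders differ from non-responders) also holds when MAR is true and response depends on baseline drinking, so it cannot be reversed into evidence against MAR.

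The attempts regression does use the outcome and is closer to the question. But the number of attempts is tied to how the outcome was collected. A trend could come from late responders drinking differently, from a one-question answer differing from a seven-day sum, or from answering by telephone.

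With 20% attrition expected and a target effect of 0.15 SD, the credibility of the primary result depends on missing data. Under the stated rule, ordinary covariate-dependent attrition could be reported as a threat to MAR. Silence from the same checks could be taken as reassurance that they cannot give.

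**Working it through.** **1. The protocol's own figures** (Power calculation). n per group = 2(1.96 + 0.8416)² / 0.15² = 697.7, so 698. The t-test version gives 698.6, so 699, as stated. 699 / 0.80 = 873.75, so 874 per group and 1748 in total, as stated. Expected responders: 1748 × 0.80 ≈ 1398. Expected non-responders: 1748 − 1398 = 350.

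**2. What the response-pattern checks can detect.** For a baseline variable in SD units, SE = √(1/1398 + 1/350) = 0.060. Significance needs a difference of about 1.96 × 0.060 = 0.12 SD. 80% power needs (1.96 + 0.8416) × 0.060 = 0.17 SD. If eight baseline characteristics were compared at 5%, the chance of at least one significant result under fully random attrition would be 1 − 0.95⁸ = 0.337, or 34%. That treats the eight tests as independent. The drinking measures are plausibly positively correlated, so it is an upper limit.

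**3. How those checks behave.** Simulation with 1748 participants, 80% response, true effect −0.15 SD, analysis adjusted for arm and baseline consumption, and 2000 trials per scenario. Assumed, because the protocol gives no values: baseline–outcome correlation 0.6 and the log-odds ratios shown.

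| Response depends on | Baseline check significant | Arm check significant | Bias of adjusted effect (SD) |
|---|---|---|---|
| Nothing (MCAR) | 6% | 5% | 0.001 |
| Baseline consumption, −0.2 per SD (MAR) | 92% | 4% | 0.001 |
| Baseline consumption, −0.3 per SD (MAR) | 99.9% | 5% | −0.001 |
| Arm only, −0.4 (MAR) | 5% | 92% | −0.001 |
| Outcome residual, −0.4 per SD, both arms (MNAR) | 5% | 5% | 0.001 |
| Outcome residual, −0.6 per SD, one arm (MNAR) | 6% | 13% | −0.095 |

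The last bias is 0.095 / 0.15 = 63% of the target effect. The two MNAR rows also show that a pattern equal in both arms left the comparison unbiased, while a pattern confined to one arm did not.

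**4. Attempts and mode.** Counting contacts in order gives email 1–3, SMS 4–6 and telephone 7–16. The regression was simulated on 1398 responders, 1000 runs each. Assumed: 20% or 35% answer by SMS or telephone, and both later modes share one shift in the reported value.

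| True late difference (SD) | Mode shift (SD) | Regression significant, all responders |
|---|---|---|
| 0 | 0 | 5–6% |
| 0 | −0.1 | 23–30% |
| 0 | −0.2 | 70–82% |
| 0 | −0.3 | 96–99% |
| +0.2 | 0 | 70–80% |
| +0.2 | −0.2 | 3–6% |

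A mode shift alone can produce a trend, and one of opposite sign can hide a real difference. Restricted to the three email contacts, the regression was significant in 4–6% of runs in every scenario, including those with a true difference among SMS and telephone responders. Email-only analysis therefore avoids the mode artefact but cannot see the latest responders.

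**5. Baseline drinking in the attempts regression.** When attempts depend only on baseline consumption, which is MAR, the regression was significant in 100% of runs without baseline consumption in the model and in 4–6% with it.

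**The case against.** The protocol's wording is cautious. It sets out to explore how plausible MAR is and speaks of possible evidence. No decision depends on the result, since the adjusted analysis is primary whatever the checks show. Complete-case analysis is described as the initial handling, and an unseen analysis plan may hold more. All of this stands and limits the harm to interpretation. It does not repair the inference, which points to the wrong assumption however softly it is put.

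The baseline comparison is also useful. Relationship status, baseline heavy episodic drinking, estimated blood alcohol concentration and negative consequences are outside the adjusted model by default. If they predict both response and outcome, that complete-case model may be inadequate, and the unadjusted analysis is more exposed still. This stands too, but the response is to condition on them; they do not show MNAR.

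Some stronger readings are tempting but not supported:

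- **The regression pools the arms and omits covariates.** The article does not specify its terms. They are unstated, not shown to be absent.
- **Telephone uses a new instrument.** The wording of the telephone item is not given. The single question is explicit for SMS; for telephone only the change of mode is.
- **More than three contacts fixes the mode exactly.** The article does not define an attempt or say that the email link closes once SMS begins.
- **Even small baseline differences will be significant.** About 0.12 SD is needed, and 80% power needs about 0.17 SD, more than the trial's target effect.

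**Conclusion.** The concern holds as an error of inference together with a confounded check. Differences in response by arm or baseline bear on MCAR. Those in arm, baseline consumption, age, university or gender are already conditioned on in the primary model, and those in other variables show which covariates may be needed. The attempts regression is the more relevant check, but a trend in it cannot be attributed to late response alone, because mode changes along the same sequence.

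The percentages illustrate behaviour under assumed correlations, missingness strengths and mode shifts. The size and direction of any mode effect in this trial are unknown. The masking result uses shifts that cancel exactly.

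A reader might go further and infer that the whole procedure fails or that the primary result is invalid. The documents do not support this. The attempts regression was not simulated under the one-arm MNAR scenario, it keeps some value, and neither the primary estimate nor the sample size depends on these checks. The point should be corrected because, with 20% attrition expected, it changes what can be said about the robustness of the result.

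**What to change.** 1. **Reword the conclusion.** State that associations of response with arm or baseline characteristics are evidence against MCAR. Add the predictors of response that are outside the planned covariates to the outcome model, or to an imputation model, as a sensitivity analysis.
2. **Specify the attempts regression.** Keep all responders, since the latest ones are those the check relies on. Adjust for arm and the planned baseline covariates and add a contact-mode term. Report alongside it the email-only result and the SMS and telephone responders by arm. An arm-by-attempts term is a useful addition, because a pattern that differs by arm is what biases the comparison. The mode term separates the trend within a mode from the step between modes; the step itself still mixes mode with lateness and should be described that way.
3. **Address MNAR directly.** Use a sensitivity analysis that varies the assumed outcome of non-responders by arm, such as delta adjustment. If the analysis plan already contains one, refer to it here.

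The cost is rewording and a little extra analysis, provided that contact mode and attempt number are stored with each response. No new outcome data are needed and the sample size does not change.

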### Power calculation

To detect an effect size of 15% standard deviations between the two groups at the 3-month follow up with a 5% significance level and 80% power, we require 699 individuals analysed per group, i.e. a total of 1398 individuals. Assuming a 3-month follow-up rate of 80%, we need 874 per group, i.e. a total of 1748 individuals.

## Discussion

Although heavy drinking of alcohol has significant health risks and presents negative social consequences, excessive drinking among university cultures is still a real problem (Thomas et al, in press). Student cultures with heavy drinking as the norm are prevalent both in Sweden and internationally. Considering the significant problem with heavy drinking in student populations, there is a need for the development and evaluation of accessible full-scale interventions that can reach a large proportion of the student population.

Previous studies have shown that a variety of automated Internet-based interventions have small, albeit significant, effects on a student’s drinking short term [16, 17, 19–22]. Thus, there is a need to further develop and evaluate new ways of reaching the large number of students who drink excessively.

Supporting evidence for the effect of SMS-based interventions is emerging; however, recent reviews have shown the need for RCTs that include larger sample sizes. This study will contribute with relevant knowledge on the effect of automated SMS support in student populations.

### Trial status

At the time of manuscript submission the recruitment of participants had not yet commenced; however, all plans and preparations for the trial were put in place.

## Abbreviations

eBAC: Estimated blood alcohol concentration
HED: Heavy episodic drinking
RCT: Randomized controlled trial
SHC: Student Health Centre
SMS: Short message service
SPIRIT: standard protocol items: recommendation for interventional trials
